## Study population

Urban setting. Primary care (PC), extrahospitalary (E) and hospital specialties (H).

Integrants of the FRIDEX cohort. Randomised sample (simple computerised randomisation stratified by sex) of men and women from 40 to 90 years of age in the FRIDEX cohort for 10 years since the baseline DXA and QRF. At the end of 2009 this sub-cohort included 5,813 persons recruited from January 1 to December 31, 2000.

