## Eligibility Criteria

A total of 3,684 subjects were randomised, 9.3% being males to maintain the original proportion of the global study cohort.

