## Exclusion criteria

Subjects < 40 or > 90 years of age at the time of the first DXA and QRF were excluded since FRAX™ does not allow the calculation of the adjusted risk outside this age range. Patients with physical or psychic limitations impeding their participation and whose relatives did not accept to respond to the TQ were excluded as were those with Paget's disease, cancer with bone involvement or disease which may simulate osteoporosis (i.e. myeloma). Patients of ethnic groups other than Caucasian were not included since other studies have demonstrated different risk characteristics. Patients not providing consent to respond to the TQ and those without a telephone to contact or did not respond after 3 calls made at different times according to the procedure manual were also excluded from the study.

Sample Size (figure 1):

For the main objective (predictive validation of FRAX™ it has been calculated that a sample of 1,070 individuals are needed in a bilateral contrast to guarantee that the sample estimates the percentage of incidence of new fractures with a precision of 3%. If an annual loss rate of 1% during the 10 years of follow up of the study is considered, a sample of 1,177 subjects is required. In the pilot study carried out in April 2009 in a randomised sample of 149 cases with three telephone calls / person, 47 persons could not be contacted (31.5%). One hundred two (68.5%) were contacted, of which 3 (4.9%) living patients and the relatives of 2 dead patients refused to participate. Cases receiving anti-osteoporotic drugs and/or those with cancer (35 people) and 6 males were excluded. Information was obtained on data at 10 years in 97 of the 149 cases. A total of 3,664 individuals should therefore be contacted, thus our population of 5,813 subjects potentially eligible guarantees the necessary sample size.

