### Analysis plan

The characteristics of the population will be described according to univariate descriptive analysis. Simple comparisons of the baseline characteristics will be made among the participants and non participants of the cohort. The Chi-square test will be used to evaluate the association between qualitative variables. The Student's t-test or, if necessary, its non parametric equivalent, the Mann-Whitney U test, will be implemented to evaluate the differences in the distribution of a quantitative variable according to the categories defined by a binary exposure. To assess the differences in the distribution of a quantitative variable according to the categories defined by a categorical variable with more than 2 categories, ANOVA analysis of variance or its corresponding non parametric test (Kruskal-Wallis) will be used.

For the predictive validation of the FRAX™ tool, the appearance of the first fracture occurring during the follow up period will be taken into account. The validation of the results obtained with the FRAX™ will be performed with the Hosmer-Lemeshow test and the calculation of the ROC curve. This test divides the participants into groups (normally 10) based on their estimated risk of fracture (FRAX™) and confirms that each group presents a number of cases of incidental fractures adjusted to the predicted number. On the other hand, the ROC curve considers the scale of FRAX™ risk as a diagnostic test of the presence of future fractures and as such leads to different calculations of sensitivity and specificity changing the cut off point selected. Finally, both probabilities (sensitivity and the complementary of specificity, or 1- specificity) will be graphically represented the curve. The shape of the curve is a visual indicator of the quality of the diagnostic test.

To know the distribution of the factors associated with fracture according to age and sex, bivariate combinations will be used with the Chi-square test among categorical variables and the Student's test among quantitative and categorical variables. To model the number of fractures occurring in our dataset which is, in fact, a count over time, Poisson regression will be used, which is what is precisely required for this type of variables and was used for the creation of the FRAX™ scale. All the statistical tests will be undertaken with a confidence interval of 95% and with the use of the 17th or latest version available of the SPSS statistical package.

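### The FRAX validation is specified with no split by sex in a sample with 9.3% men, and the pilot removes males, so it is unclear whether men are validated; if they are, a two-fold error in men would probably be missed

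*Protocol article*

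**What the plan says.** - **Sampling.** Study population describes the sample as "Randomised sample (simple computerised randomisation stratified by sex) of men and women from 40 to 90 years of age". Eligibility Criteria adds: "A total of 3,684 subjects were randomised, 9.3% being males to maintain the original proportion of the global study cohort".
- **Sample size.** The paragraph under Exclusion criteria sizes the study for one overall fracture incidence: "a sample of 1,070 individuals are needed in a bilateral contrast", "with a precision of 3" percentage points. No size is set for either sex.
- **Pilot.** The same paragraph starts from 149 people, obtains 10-year data on 97, and removes 35 (anti-osteoporotic drugs and/or cancer) and 6 males. The text after Figure 1 carries the remaining 56 (37.6%) into the calculation of how many people to contact.
- **Validation.** The Analysis plan states: "The validation of the results obtained with the FRAX™ will be performed with the Hosmer-Lemeshow test and the calculation of the ROC curve". It adds that participants are put into groups, normally 10, by their FRAX risk. Sex is named only later, for describing how factors associated with fracture are distributed.
- **Scope of the conclusion.** The main objective refers to a Spanish population without separating the sexes. The limitations section extends the results to people assessed by case finding, with no restriction by sex.

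**The concern.** Two things do not fit together. First, the sample is built to keep men at 9.3%, yet the pilot yield that justifies the number of contacts is calculated after males are taken out. A reader cannot tell whether men belong to the validation set.

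Second, if they do belong, the stated method hardly sees them. Groups formed by FRAX risk mix about 9 men with 91 women in every 100 people, so a fault confined to men is diluted in both the group counts and the ROC curve. The article gives grounds not to assume that the sexes behave alike. In Table 1 the men are older (mean 65.0 against 60.8 years) and more often have a previous fracture (35.6% against 25.7%). The Background calls osteoporosis in men under-diagnosed, with more severe consequences. The Discussion cites studies in which FRAX predicted fewer fractures than were observed. A satisfactory overall result could therefore be read as covering men when it says little about them.

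**Working it through.** **1. The plan's own figure.** Precision formula for one proportion: n = z² p(1 − p)/d². With z = 1.96, d = 0.03 and p = 0.5 (assumed; the article gives no p), n = 3.8415 × 0.25/0.0009 = 1,068, against 1,070 stated. With 10% added for losses, 1,070 × 1.10 = 1,177, as stated. The target is one overall incidence.

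**2. The pilot chain.** 149 − 47 not contacted = 102; 102 − 3 − 2 refusals = 97; 97 − 35 − 6 = 56; 56/149 = 37.6%. If the 35 are removed first, 62 remain, and 9.3% of 62 is 5.8. Six males is thus about the number expected if every remaining man was removed, although the article does not say so.

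**3. Men available, if men are included.**
- 0.093 × 1,070 = 100
- 0.093 × 1,177 = 109
- 0.093 × (3,664 × 56/149 = 1,377) = 128

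The 37.6% yield is only a rough guide for men, because it was calculated after males were removed. Putting the six back gives 62/149 = 41.6%, and 0.093 × (3,664 × 62/149 = 1,525) = 142, so the order of size is unchanged. Using 3,684 (Eligibility Criteria) instead of 3,664 also changes little.

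**4. Dilution of the overall ratio.** Let s be the share of expected fractures that falls in men, and k the ratio of true male risk to FRAX, with FRAX correct in women. Then overall observed/expected = 1 + s(k − 1).

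| Mean FRAX risk, men relative to women (assumed) | s | k = 2 | k = 0.5 |
|---|---|---|---|
| equal | 0.093 | 1.09 | 0.95 |
| half | 0.0465/0.9535 = 0.049 | 1.05 | 0.98 |
| 1.5 times | 0.1395/1.0465 = 0.133 | 1.13 | 0.93 |

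**5. Simulation.** There were 1,500 runs per scenario, with N = 1,070 or 1,378, 9.3% men and FRAX correct in women. Mean 10-year risk was assumed at 5-20%, with men's mean equal to or below women's. The 10-group test uses 10 degrees of freedom because FRAX is not fitted to these data.

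| True male risk | Overall observed/expected | Overall test rejects, N = 1,070 | Overall test rejects, N = 1,378 |
|---|---|---|---|
| equal to FRAX | 1.00 | about 4-7% (both N) | |
| twice FRAX | about 1.05-1.10 | 9-19% | 11-22% |
| half FRAX | 0.95-0.98 | 4-6% (both N) | |

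With 8 degrees of freedom, rejection for the doubling rises to 17-35%, but a correct FRAX is then already rejected in about 9-13%. The overall AUC moves by at most about 0.02. A test of the overall observed/expected ratio, which the plan does not name, rejects the doubling in about 10-42% at N = 1,378.

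**6. The same data analysed in men only.**

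| | About 100 men | About 128 men |
|---|---|---|
| Doubling, observed/expected test | 61-99.8% | 68-99.9% |
| Doubling, 5-group test | 56-98% | 60-99.7% |
| Halving, observed/expected test | 13-77% | 19-90% |
| Halving, 5-group test | 2-33% | 1-49% |

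**7. Precision in men.** The 95% half-width for incidence in 100 men is 1.96 × √(p(1 − p)/100): 4.3 points at p = 5%, 5.9 at 10% and 7.8 at 20%, against the overall target of 3. If observed and expected agree, the exact Poisson interval for observed/expected is 0.37-2.18 with 6 fractures (about 5% of 128) and 0.50-1.79 with 11.

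**The case against.** The best defence is that this argues from silence. The Analysis plan names methods, as a condensed article does, and never says that they will be applied only once to both sexes together. Analyses by sex may stand in a fuller document that is not shown. A reader might infer that one pooled result will be reported as valid for both sexes, but no sentence says so.

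Nor does stratified sampling promise validity by sex. The stated purpose is "9.3% being males to maintain the original proportion of the global study cohort", and proportional allocation followed by an overall analysis is coherent and needs no weights. Any overall test can hide an error in a 9% subgroup, and nothing in the article shows that FRAX is wrong by a factor of two in men. If the pilot exclusion means that men are left out of the validation, the dilution does not arise.

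Much of this stands, and it limits the wording. It does not remove the point. The section goes into enough detail to fix the grouping variable as FRAX risk alone, and it names sex for one analysis but not for the main one. Whether or not men are in, something has to change: results by sex are needed if they are, and a conclusion limited to women is needed if they are not.

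**Conclusion.** The point holds conditionally. The article does not settle whether men are in the validation set. If they are, the specified test would probably miss a two-fold FRAX error in them: in about 78-91% of studies when male risk is doubled, and in about 94-96% when it is halved, where rejection is no more than chance. A reader might infer that such an error is certain to be missed. That is too strong, since the overall test rejects a doubling in 9-22% of runs.

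These figures rest on assumed mean risks of 5-20%, an assumed spread of FRAX risk, and a male mean no higher than the female one. With higher male risk, which Table 1 does not rule out, dilution is milder (1.13 in the third row of the first table), and the rejection rate was not simulated. Separate analysis helps but does not fully resolve the matter: 100 to 130 men can show a doubling reasonably well and a halving poorly.

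**What to change.** 1. Reconcile Study population, Eligibility Criteria and the pilot description by stating whether men enter the FRAX validation, and why the pilot yield was calculated after removing 6 males.
2. If men are included, add to the Analysis plan that observed/expected and AUC, each with a 95% CI, will be given separately for women and men. Women form the main validation, and men are reported as imprecise.
3. If men are not included, or if their interval is too wide to be informative, limit the conclusion to women.

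The cost is a sentence or two of text, two extra tables and a weaker statement about men. No new data or calls are needed, and the selection already reported as done stays as it is.

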### Study limitations, potential limitations and biases

Since the FRIDEX cohort is constituted by subjects requiring a DXA scan (according to their physician), it likely that the recruited population will be at a baseline risk greater than that of the general population. Nonetheless, descriptive analysis of the population of this cohort indicates that the percentage of 32.3% of persons with densitometry osteoporosis is very similar to that reported in the literature for women of 50 years of age. Our results may therefore be extrapolated to a population in which the physician is evaluating the risk of low bone mass or fracture (case finding) which is, furthermore, the population recommended for investigation by the WHO.

The QRF used includes the variables of the FRAX™ scale and is complemented by the follow up telephone questionnaire on fractures, falls and new medications prescribed as well as diseases developed in the last 10 years.

The variable "number of falls" was not collected at the beginning of the FRIDEX cohort. Therefore, it may only be considered as an outcome variable in the subgroup of cases with incidental fractures posterior to the collection of this variable. Nonetheless, according to the opinion of the external assessor and the research team, this variable is highly related to the risk of fracture and thus, should be collected and taken into account in this study.

To minimise the effect of possible losses which may imply bias (given the morbimortality associated with fractures and the possible dropouts over 10 years), notable increases in the sample size have been considered necessary such as the cases to be localised among those with a contact telephone number. We believe that this will minimise the losses to follow up or refusal to participate for several reasons: information will be collected by telephone to avoid the difficulties of post questionnaires, which have low response rates in our setting; in addition the participants in the FRIDEX cohort had already accepted to participate in the QRF and almost all of the persons contacted in the pilot study accepted to answer follow-up survey.

There may be a bias in the collection of the information on incidental fractures which is collected based on the patient self-report. Nevertheless, in this study all the new fractures detected will be contrasted with the corresponding medical reports or by consultation with the physicians. Thus silent vertebral fractures will be scarcely detected but the symptomatic vertebral fractures, which are those included in the prediction of the FRAX™, will be collected. In addition, this is the usual method used in large epidemiological studies. The possible limitations inherent to data collection by telephone will be minimised with interviewer training among personnel with health care background through the improvement detected in the pilot study and by the incorporation of potential improvements thereafter.

The study has been approved by the ethical committee of the Clinical Research Ethics Committee of the Vall d'Hebron University Hospital (Barcelona, Spain). Additional file 3 shows the timing of the project.

## Discussion

Since more than 10 years ago numerous reports have recognised the importance of other risk factors for new osteoporotic fractures in addition to low BMD. This new evidence has modified the conception of the utility of BMD as the gold standard or as an added element for decision making in the management of osteoporosis in primary health care settings.

The FRAX™ tool was published by the WHO in 2008 and was created to establish a calculation of the probability of absolute risk of osteoporotic fracture at 10 years. This was initially based on the analysis of thousands of person included in several cohorts in Europe [12,13]. Since its publication this tool has also been used to know the risk of fracture in other population cohorts in Europe, the United States of America, Canada, and Japan [25-30]. Likewise, since its publication this tool has undergone new adjustments and calibrations for different populations [30]. On the other hand, some studies have also recently been published, in which the cases of fracture estimated or expected by the FRAX™ tool were significantly lower than the cases of incidental fractures actually observed in the 10 years of follow up [31].

In the case of the Spanish population included in the FRAX™ tool, there are some doubts as to their representativeness because of the scarce response of original study and scarce global number of patients included [12,13], which could represent problems of external validity and should be contrasted with new studies of large cohorts over long periods of follow up to allow the establishment of epidemiological relationships adjusted to each population.

The extension of a method for calculating the risk (probability) of fractures using the FRAX™ tool is foreseeable in Spain similar to what is occurring in other countries and this would justify a study such as this to allow the necessary adjustments in calibration of the parameters included in the logarithmic formula constituted by FRAX™.

From the point of view of validation and economic analysis of the FRAX™ tool, the National Osteoporosis Guideline Group (NOGG) has recently published a calculation with FRAX™ which takes cost-effectiveness to avoid a new fracture in a population in the United Kingdom into account [15]. This is one of the first countries to publish studies on the economic cost which means the willingness to pay and cost-effectiveness to avoid a new fracture in its population. These calculations have been based on the calculation of fracture risk using the FRAX™ tool and determined clinical risk factors.

It can be expected that other counties will establish the same parameters with economic evaluation derived from the application of the FRAX™ tool. A study of the diagnostic validation of the FRAX™ tool is necessary as the first step to establish the criteria of cost-effectiveness and the number of cases to treat to avoid the appearance of new osteoporotic fractures.

Studies in large cohorts over long periods of follow up have allowed epidemiological associations to be established, and although numerous studies have demonstrated the independent association of clinical and environmental risk factors with low BMD, some associations with fractures in populations in different geographical zones are pending thus, the need for extensive epidemiological studies in the Spanish population.

One of the few studies published with the FRAX™ tool in Spain did not provide new knowledge on the idealness of the cohorts represented [32], thereby justifying a study such as the present which will allow the necessary calibrations and adjustments of the parameters included in the logarithmic formula constituted by the FRAX™. At the same time, the scientific community requires a relatively easy and agile system to determine when a DXA should be requested and/or when treatment for osteoporosis should be initiated based on reliable predictive models similar to those already implemented in the daily routine for the prevention of cardiovascular events.

The WHO has recommended that prospective studies should be performed with this methodology in our population. This is therefore a great opportunity to validate and contribute to the determination of its true utility among the collective of physicians, especially in Primary Care, and in the population by focusing on interventions in the cases of greatest risk of fracture.

## Ethics

The study has been approved by the ethical committee of the Clinical Research Ethics Committee of the Vall d'Hebron University Hospital (Barcelona, Spain).

Telephone calls will be made to all the cases of the randomised sample of the cohort. According to the protocol accepted by the reference Clinical Research Ethics Committee [PR registration number (AG) 68/2009], verbal consent will be requested at the onset of the study to continue with the telephone interview, the posterior follow up calls and to compare the fractures in the medical records.

The investigators guarantee and will be responsible for data confidentiality. The clinical data will be introduced into a computerised database in which the patients are identified by an anonymised code. A parallel database will be created containing the data of patient affiliation and the corresponding relational code. Only the Principal Investigator and the study data manage will have access to this database.

## List of abbreviations

AATRM: Agència Avaluació Tecnologia i Recerca Mèdiques (Catalan Agency for Health Technology Assessment and Research); BMD: Bone Mineral Density; COPD: Chronic Obstructive Pulmonary Disease; DB: Database; DXA: Dual-energy X-ray Absorptiometry; E: Extrahospitalary specialties; FRAX™: Fracture Risk Assessment tool; FRIDEX: Factors of Fracture Risk and Bone Densitometry DXA cohort; H: Hospital specialities; ISCD: International Society for Clinical Densitometry; NAHNES: National Health and Nutrition Examination Survey; NOGG: National Osteoporosis Guideline Group; PC: Primary Care; QRF: Questionnaire of Risk Factors; RF: Risk Factor; RR: Relative Risk; SEIOMM: Sociedad Española Investigacion Osea y Metabolismo Mineral (Spanish Society for Bone and Mineral Research); TQ: Telephone Questionnaire: follow up; WHO: World Heath Organisation.
